### Process evaluation (Objective 2)

The process evaluation will be informed by both qualitative and quantitative studies to gain a better understanding of what the intervention consisted of, the extent to which it was implemented as planned, and how well 3PLs functioned within the health system. Trained researchers in the different disciplines will implement the quantitative and qualitative studies separately but alongside each other, and the different teams will share findings throughout the course of the work to inform each other’s data collection.

Quantitative monthly indicator data from the implementer will be analysed to examine to what extent different components of the intervention were implemented as intended. The main indicators of interest will relate to timeliness of deliveries, achievement of stock-out rates below the 2 % target, and availability and use of data for informing stock orders (Table 2).

**Table 2 Tab2:** Indicators used for process evaluation

Indicator	Data source
1. Intervention roll-out	
Percentage of SDPs^a^ receiving FP^a^ product through intervention (%)	Monthly data from implementing organisation
2. Timeliness of visits	
Percentage of 3PL^a^ visits conducted after scheduled date (%)	Monthly data from implementing organisation
Percentage of requests for emergency re-supply followed by unscheduled 3PL visit within 3 days (%)	Monthly data from implementing organisation
3. Stock-outs	
Percentage of 3PL visits with stock-outs observed (%)	Monthly data from implementing organisation
4. Data availability and use	
Percentage of SDPs with data for all 3PL visits (%)	Monthly data from implementing organisation
Percentage of SDPs with correct data for all 3PL visits compared to stock card information (%)	Monthly data from implementing organisation
Percentage of 3PL visits with complete information for date and products (%)	Monthly data from implementing organisation
Percentage of 3PL visits where the calculated quantity is delivered (calculated as three months’ average consumption minus stock available) (%)	Monthly data from implementing organisation

^a^
*SDP* Service Delivery Point; *FP* Family planning; *3PL* Third-party logistician

Qualitative data collection will be conducted at all levels of the health system (Fig. 5) by trained anthropologists, supervised by senior academics with in-depth knowledge of the context. A discourse analysis of funding documents, proposals and project reports related to the intervention will be conducted to refine the initial theory of change elaborated by the research team.

**Fig. 5 Fig5:**
[figure not shown]
Data collection methods used in the ethnography of the supply chain

Repeat in-depth interviews will be conducted with key national and international stakeholders, during and immediately after the implementation period, to allow researchers to develop a rapport with interviewees, improve data quality and monitor change over time. These interviews will focus on the development of the project, implementation issues and lessons learned, to understand how closely the implementation followed the intervention design laid out in the theory of change. In-depth interviews will also be conducted with all cadres of personnel involved in the supply chain and FP at the regional, district and SDP levels (including SDP staff, programme auditors and 3PL), to examine the acceptability of performance-based contracting, how the intervention was modified in different contexts, and potential unanticipated issues. In-depth interviews will be administered using topic guides, which will be piloted and developed iteratively as data emerge.

Three repeat in-depth interviews will be conducted over the evaluation period with up to 10 key informants at the national level. In-depth interviews will be conducted with regional medical officers (up to 11), key implementing staff at the regional level (up to 15), 3PLs and auditors (up to 10), as well as with key stakeholders from the national (*n* = 1) and regional storerooms (*n* = 11), district stock managers (*n* = 11), health workers (*n* = 60) and pharmacists (*n* = 10). Up to 160 in-depth interviews will be conducted in total; the final sample size will follow the principle of saturation, wherein data collection continues until new data do not shed further light on the research questions. Sampling for interviews will be purposive to represent urban and rural areas and the diverse types of SDPs as well as distance from regional medical storerooms, and time since introduction of the intervention.

Ethnographic work will be carried out to understand the logics and practices of implementation on the ground. Researchers will travel with 3PL while performing deliveries and carrying out stock inventories, and observe the lived realities of both 3PL and SDP staff. Transcripts of interviews and field notes will be translated and independently coded by researchers in London and Senegal using qualitative software. Coding will be undertaken along key themes that are being explored, allowing for unexpected issues that emerge, and jointly discussed by the qualitative team to come to a consensus on major findings.

In addition, we will ask 25 SDP managers to fill in fortnightly reflective diaries on issues relating to the implementation, giving them a voice to identify unanticipated issues to the research team. Preliminary findings from the diary study will be fed back to SDP managers to validate our interpretation of their writings and to give them a further opportunity to discuss collectively their perspectives on the project. Similarly, findings from all objectives will be presented to key stakeholders at several points throughout the evaluation, in order to check the validity of results and elicit potential reasons for these.

### Assessment of contextual factors (Objective 3)

The purpose of this component of the evaluation is to understand what factors influence the effect of stock availability in SDPs on contraceptive use among women, using exploratory qualitative and quantitative methods. We hypothesise that FP uptake in areas with contraceptive availability would be higher in areas with high-quality FP services, where women have better geographical and financial access to contraceptive services, and with more FP-related activities (other than the intervention), such as demand-generation activities. Therefore, several approaches will be used to assess the quality of FP services provided in SDPs, describe women’s physical access to FP services, and estimate the implementation intensity of other FP­related activities in regions throughout Senegal, in order to examine whether the effect of the intervention varied according to these factors.

First, the quality of FP services will be assessed using data from the Service Provision Assessments [46], which collect information on choice of methods offered, observations of FP consultations and exit interviews with clients and providers. An index of FP service quality will be developed based on frameworks developed by Bruce, Mauldin and Ross [33, 50], as well as other existing indices [51–55]. The median quality of FP services across SDPs will be calculated for each region of Senegal, and any observed regional differences in the change in MCPR (objective 1) will be interpreted in light of regional FP quality category (high, medium, or low)..

Second, GPS information for all SDPs in Senegal will be obtained from the Ministry of Health, coordinates for regional storerooms taken during fieldwork and road shape files obtained from ESRI [56]. QGIS software [57] will be used to map SDPs, storerooms and roads. The 2013 census data [58] will be used to overlay age-specific fertility rates on SDP points, and buffer zones created to determine where women do and do not have access to SDPs providing FP, SDPs with FP stock available and SDPs with high quality FP services. These results will be used to examine whether changes in stock availability have had a larger impact on MCPR in regions where women have better access to FP services. In addition, in-depth interviews will be conducted with women to triangulate these quantitative analyses, with the aim of understanding the barriers they face in accessing FP, the quality of care they experience in SDPs, and what aspects women value when seeking care in public SDPs (cost, counselling, availability of methods etc.).

Third, indicators to measure implementation intensity of FP-related activities (other than the intervention) will be developed using Heidkamp et al’s “snapshot” approach [59]. These indicators will be informed by in-depth interviews with different FP actors in Senegal (see Process evaluation), and calculated based on policy documents and reports from these organisations for each region. Results from the impact evaluation (objective 1) will be stratified by region according to the intensity of other FP-related activities in order to examine whether the effect of the intervention on contraceptive use was stronger in regions with other FP programmes active at the same time as the intervention.

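### One access layer used to test effect modification in Objective 3 is defined by contraceptive stock, which the intervention itself changes; the quality index may share the overlap

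*Protocol article*

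**What the plan says.** The section on contextual factors (Objective 3) names service quality, women's access and the intensity of other family planning activity as factors to be assessed "in order to examine whether the effect of the intervention varied according to these factors".

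- **Access.** Facilities, storerooms and roads are mapped, with "buffer zones created to determine where women do and do not have access to SDPs providing FP, SDPs with FP stock available" and, as a third layer, high-quality facilities. The mapping results are then meant for judging "whether changes in stock availability have had a larger impact on MCPR in regions where women have better access to FP services".
- **Quality.** The source is the Service Provision Assessments (SPA), "which collect information on choice of methods offered, observations of FP consultations and exit interviews with clients and providers". The plan's next step is a composite score: "An index of FP service quality will be developed based on frameworks" and other published indices; its items are not given. Every region then receives a single summary value: "The median quality of FP services across SDPs will be calculated for each region of Senegal". That value is turned into one of three levels (high, medium, low), and the plan adds that "any observed regional differences in the change in MCPR (objective 1) will be interpreted in light of regional FP quality category".
- **Other activity.** The intensity indicators expressly leave the intervention out.

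Neither the quality index nor the stock layer is dated. The outcome and impact section (Objective 1) makes stock availability the outcome of objective 1.1, and the description of the intervention gives better availability as its aim.

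**The concern.** An effect modifier should describe the setting in which the intervention acts, not something the intervention produces. The stock-based access layer fails that test on the face of the text: facility stock is the exposure whose effect is studied and also part of the variable used to subdivide that effect. The layer of high-quality facilities, and the regional quality category, would fail it too if method-choice or availability items from the SPA enter the index.

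A difference in MCPR change between better- and worse-ranked regions could then be read as evidence that supply works better, or worse, where services are good. It might reflect only how much stock a region had, or gained. That reading matters to a ministry deciding where supply improvements need to be paired with other investment.

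**Working it through.** The document gives no figure for this comparison, so there is none to reproduce. The check is a reading of the text plus an illustration on assumed values.

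**1. Overlap in the text.** Exposure in the access question: change in facility stock. One component of the access modifier: facilities with stock. Outcome of objective 1.1: facility stock. For access the overlap is explicit. For quality, the SPA is said to record the choice of methods offered, but a method being offered is not the same as its being in stock, and the index items are unknown. There it is conditional.

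**2. Model with no true modification.** Assumptions, none from the protocol except the number of regions (14): baseline availability b between 0.30 and 0.70; the intervention closes a fraction c of the remaining gap; every region has the same response per unit of stock.

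- gain = c × (1 − b)
- post-rollout availability = b + gain
- MCPR change (points) = 3 + 15 × gain

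**3. Why the sign is not fixed.** Two comparisons by hand:

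| b | c | gain | post-rollout availability | MCPR change |
|---|---|---|---|---|
| 0.50 | 0.10 | 0.10 × 0.50 = 0.050 | 0.550 | 3 + 15 × 0.050 = 3.75 |
| 0.50 | 0.90 | 0.90 × 0.50 = 0.450 | 0.950 | 3 + 15 × 0.450 = 9.75 |
| 0.30 | 0.94 | 0.94 × 0.70 = 0.658 | 0.958 | 3 + 15 × 0.658 = 12.87 |
| 0.70 | 0.94 | 0.94 × 0.30 = 0.282 | 0.982 | 3 + 15 × 0.282 = 7.23 |

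In the first pair closure differs, and the region with more post-rollout stock shows the larger MCPR change (9.75 against 3.75). In the second pair closure is equally high, and the region with more post-rollout stock shows the smaller change (7.23 against 12.87), because it had less to gain.

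**4. Simulation.** 14 regions, 20,000 runs per setting, noise SD of 1 point in MCPR change. The modifier index is w × stock + (1 − w) × unrelated quality, both standardised. The result is the mean MCPR change in the top five regions minus that in the bottom five; the true value is 0.

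| Stock in the index | Gap closed | w = 25 % | w = 33 % | w = 50 % |
|---|---|---|---|---|
| post-rollout | 10–90 % | +0.8 | +1.1 | +1.8 |
| post-rollout | 90–98 % | −0.4 | −0.6 | −0.9 |
| none | either | 0 | 0 | 0 |

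Pre-rollout stock in the index at 10–90 % closure gives about −0.5 (w = 25 %) to −1.3 points (w = 50 %).

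If the components are not standardised, the post-rollout artefact at 90–98 % closure is below 0.1 point in size. At 10–90 % closure it is smaller than in the table but still positive.

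A second set of assumptions (baseline mean 0.50, post-rollout mean 0.90, 0.10 points of MCPR per point of stock, w = 25 to 50 %) gives +0.2 to +1.4 points with post-rollout stock, −0.7 to −1.7 with pre-rollout stock, and 0 without stock.

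**5. Scale.** The study setting section reports national MCPR of 12 % in 2010–11 and 16 % in 2012–13, a rise of 16 − 12 = 4 points. An artefact of 1 to 2 points would be visible against that.

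**The case against.** The case on the other side has real weight.

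- **Timing.** A reader might infer that quality and access are measured after rollout. The text does not say so: it gives no date, SPA rounds are annual, and a condensed article may leave the choice of round to the full protocol or analysis plan. The missing date is not itself a finding.
- **Direction.** A reader might infer that regions where stock rose most will be ranked higher, creating a spurious benefit of quality. That does not follow. The intervention section reports stock-outs eliminated in the pilot district and below 2 % of days in Dakar within 6 months, and the process evaluation uses a 2 % target. These are early or target figures, but under near-complete closure the sign reverses.
- **The question asked.** The access question concerns the impact of a given stock change. In the model above, once each region's stock gain is accounted for, the artefact is 0.0 at every weight. This stands: the artefact belongs to comparisons of MCPR change that do not account for stock gain. The quality comparison is worded that way; for access, the text does not say how gain would enter.
- **Mainly geographic access.** Table 4 lists only facility coordinates and census data for access, and two of the three layers are not defined by stock. But the Methods text names the stock layer and sends the mapping results to the modification question without excluding it.
- **Status.** Objective 3 is exploratory, Table 4 calls the quality and access analyses descriptive, and interviews with women triangulate the results. This limits the consequence but does not remove the overlap.

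**Conclusion.** The point holds for the stock-based access layer, on the current text. It holds conditionally for the quality index and the high-quality-facility layer, if method-choice or availability items are included. Such a modifier can show a gradient in MCPR change where none exists: about −0.9 to +1.8 points with post-rollout stock, negative with pre-rollout stock, and zero without stock. These figures rest on assumed baseline availability, gap closure, stock share of the index and MCPR response, so they show that the artefact is possible and that its sign is open; they do not predict its size here.

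It would go too far to say that Objective 3 as a whole gives a biased answer. The intensity measure excludes the intervention and the qualitative work is untouched. The consequence is confined to the access comparison and possibly the quality comparison. Severity is minor and confidence moderate.

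**What to change.** - For effect modification, define access by the stock-free layers already planned: distance or buffers to facilities offering family planning.
- List the quality index items. Compute the index with and without method-choice and availability items, and use the version without them as the modifier, including for the high-quality-facility layer.
- Take that version from a pre-rollout SPA round where one exists, and flag regions without one. Pre-rollout timing alone is not enough, because baseline stock is tied to the room for gain and produces a negative artefact.
- Report maps of facilities with stock as descriptive outcomes of objective 1.1, or treat stock as a mediator.

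The cost is rewording and recoding of data already in the plan. The downside is a narrower quality index and possibly fewer SPA facilities per region. The article does not give the first SPA round, so how many regions have a usable pre-rollout round must be checked.

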A general mixed-effects logistic regression model will be constructed using an approach similar to the stepped-wedge analysis method outlined by Hussey and Hughes [47], although the rollout was not randomised. Stock availability will be modelled as a binary outcome variable (stock present or absent on the day of the survey) for all contraceptive methods, and as an ordinal variable for the number of each of the most popular short-acting (condoms and pills), medium-acting (injectables) and long-acting methods (implants and IUDs). Time will be treated as a fixed effect, and region as a random effect, to allow the intervention effect to vary regionally. Independent covariates at regional level, such as density of SDPs offering FP services and density of road network, will be used as well as SDP-level variables such as facility type.

Similarly, to examine the effect of the intervention on contraceptive use among WRAU (objective 1.2) we will use information on contraceptive use at the population level from the Demographic and Health Surveys [48], nationally representative surveys of women of reproductive age also conducted annually. As above, a mixed-effects logistic regression model will be built treating region as a random effect, and including woman-level covariates (such as education level) and regional covariates (such as pre-intervention MCPR). For both objectives, secondary analyses allowing for a delay in the effect of the intervention will be explored by allowing the variable for the intervention mode to be fractional.

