There are several limitations to our approach. First, our ability to investigate contraceptive stock supply over time relies on the availability of good quality stock data in SDPs. Between 2010 and 2012, health staff in some regions of Senegal took strike action which manifested as a refusal to send health data to the district level, which may affect data availability for the time series study in regions where the 24-month pre-intervention period includes 2011–2012. Health facility and staff adherence to the strike was variable, and it is unclear whether stock data were particularly affected since a different cadre of staff (community-funded “dépositaires”, or stockists) is tasked with completing stock cards, rather than the centrally-funded nursing staff who were on strike. In addition, it is not clear whether, given the duration of the strike, data continued to be collected but were not sent upward or whether nursing staff and stockists stopped recording data in SDPs. The availability of good data in SDPs will be explored in the data quality pilot study prior to collecting data for the time series.

Second, estimating the contribution of the intervention to any observed increase in contraceptive use may be challenging given that other FP-related activities such as demand-generation activities, public endorsements of FP by community leaders, and outreach activities are implemented throughout the country. The evaluation methodology is designed to take this limitation into account as effectively as possible. The staggered rollout of the intervention across regions will enable us to estimate more precisely the effect attributable to the intervention. As part of the assessment of contextual factors (objective 3), we will further estimate the implementation intensity of FP-related activities in order to disentangle the potential effect of the intervention and of other FP-related activities on the MCPR.

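### Stratifying results by the intensity of other family-planning programmes examines effect modification; it does not by itself separate their effect on MCPR from the intervention's

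*Protocol article*

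**What the plan says.** The limitations in the Discussion accept that other FP activities, which run across Senegal, make it hard to attribute a rise in MCPR to the intervention. Two devices are offered. The first is the staggered rollout. The second is to estimate the intensity of other FP activities "in order to disentangle the potential effect of the intervention and of other FP-related activities on the MCPR".

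The section on contextual factors (Objective 3) says how intensity will be measured and used. The indicators are "calculated based on policy documents and reports from these organisations for each region". On their use, the same paragraph has this: "Results from the impact evaluation (objective 1) will be stratified by region according to the intensity of other" programmes. The reason it gives for splitting the results this way is the following: "examine whether the effect of the intervention on contraceptive use was stronger in regions with other FP programmes active at the same time". The opening of that section gives the same purpose for the whole component: "in order to examine whether the effect of the intervention varied according to these factors".

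In the Objective 1 section, the MCPR model follows the stock model, which has time as a fixed effect and region as a random effect. It is described as "including woman-level covariates (such as education level) and regional covariates (such as pre-intervention MCPR"). Programme intensity is not among the examples. The rollout is stated not to have been randomised. The plain-language summary says only that ways of separating the programmes' effects will be explored.

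**The concern.** Stratifying by intensity asks whether the intervention worked better in some regions than in others. Disentangling asks how much of the MCPR change would have occurred without the intervention because other programmes were growing. These are different questions, and an answer to the first does not settle the second.

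The gap matters where another programme expanded in a region at about the time that region received the intervention. Regions were not randomised to rollout dates, so nothing in the design makes such coincidence unlikely. The stock outcomes have tracer commodities as a comparison series; MCPR has no equivalent. The effect estimates from Objective 1 also feed the cost-effectiveness ratios, including the number of additional women using modern contraception, so an error in attribution would carry through to them.

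**Working it through.** The article states no sample size, power or expected MCPR effect for this analysis, so there is no figure of its own to reproduce. The check compares aim with method and then tests what stratification does under different programme timings.

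**1. Aim against method.** The Discussion's aim concerns the size of two separate effects on MCPR. The Objective 3 section's use of intensity concerns variation in one effect between regions. No stated analysis enters intensity as an adjustment in the MCPR model, and no time dimension is stated for the indicators.

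**2. Illustration.** Input from the article: the Fig. 1 caption gives rollout to 3 regions in 2013, 6 in 2014 and 5 in 2015; 3 + 6 + 5 = 14, which agrees with the 14 regional medical offices in the section on the intervention's design.

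Assumptions not in the article: yearly surveys 2012 to 2016; a common rise of 1.5 points a year; true intervention effect θ = 3.0 points, the same in every region; other programmes add γ = 3.0 points at full intensity; 7 high-intensity and 7 low-intensity regions. The model is linear and noise-free with fixed region effects, a simplification of the planned mixed logistic model:

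MCPR(r,t) = region(r) + year(t) + θ·X(r,t) + γ·P(r,t)

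X is 1 once region r has the intervention, and P is programme intensity. The estimate of θ without P is given for all regions and for each stratum; the last column adds P to the model for all regions.

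| Timing of other programmes | All regions | High stratum | Low stratum | All regions, with P |
|---|---|---|---|---|
| A. One national start | 3.00 | 3.00 | 3.00 | 3.00 |
| B. Start with each region's rollout, intensity 1 or 0.5 | 5.23 | 6.00 | 4.50 | 3.00 |
| B0. As B, intensity 1 or 0 | 4.46 | 6.00 | 3.00 | 3.00 |
| C. Same calendar ramp in high-intensity regions, mostly early-rollout ones | 3.11 | 3.00 | 3.00 | 3.00 |
| D. Start 0 to 1 year after rollout, intensity 1 or 0.5 | 4.11 | 5.25 | 2.91 | 3.00 |

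Scenario B can be done by hand. Within a stratum of intensity c, P = c·X, so the fitted coefficient is θ + γc: 3.0 + 3.0 × 1 = 6.0 and 3.0 + 3.0 × 0.5 = 4.5. The gap of 6.0 − 4.5 = 1.5 points looks like effect modification although the true effect is 3.0 everywhere.

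Scenarios A and C show the opposite. Year effects remove a national programme, and stratification removes growth that follows calendar time within a stratum. In B0 the programme-free stratum is also unbiased.

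The last column needs care. In A, P duplicates the year effects and adds nothing. In B and B0, P equals intensity times X, so adding it is the same as fitting an intervention-by-intensity interaction; 3.0 is recovered only because the true effect was set equal in all regions. Such data cannot tell a programme effect from effect modification. In C and D, programme dates differ from rollout dates, and that difference is what allows separation. Correct measurement of P is assumed throughout.

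**The case against.** The case for the plan is substantial. The Discussion names the staggered rollout first and intensity as a further step, so intensity is not the only device. With time as a fixed effect, growth shared by all regions drops out. Objective 3 is described as exploratory. The text does not say that each region gets a single undated value, and its reference to programmes active alongside the intervention suggests some dating. The covariates are given as examples, in a condensed article whose full analysis plan is not shown. Nothing in the article says that other programmes followed the rollout region by region; it describes them as countrywide.

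All of this stands, and it limits the point. It does not remove it. The point does not depend on a missing covariate list: the article states an aim for the intensity measure and states a use for it, and the use does not meet the aim.

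**Conclusion.** Beyond the staggered rollout and the time effects, the stated use of intensity does not adjust the MCPR effect for programmes whose growth differs by region and time. It therefore does not by itself deliver the disentangling promised in the Discussion. Differences between strata could reflect such confounding instead of true effect modification.

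The size of any bias cannot be derived from the article. The figures in the illustration show direction under assumed inputs, not an expected magnitude.

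A reader might infer more, but the article does not support it:

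- That stratification removes no confounding, or can never help. Scenarios C and B0 contradict this, although activity across the whole country makes a programme-free stratum unlikely.
- That the national rise in MCPR from 12 % to 16 % before most of the rollout measures the bias. It is a national figure; the part common to all regions is removed by the time effects.
- That a fixed regional score is already absorbed by the region term. Region is a random effect, which need not absorb it fully.
- That the strata are too thin. The number of intensity strata is not stated.

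**What to change.** Record dates for the activities already being abstracted from documents and interviews, so that intensity is available per region and survey year. Add it as a time-varying covariate in a sensitivity analysis of the Demographic and Health Survey stepped-wedge model, and report the intervention effect with and without it. Keep the stratified results, or use an intervention-by-intensity interaction, but label them exploratory effect modification. If dated intensity cannot be obtained, or is too collinear with rollout, narrow the statement in the Discussion to describing how the effect varied with intensity.

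The cost is some extra abstraction work and wider intervals. They could be much wider if programme growth closely follows rollout, which is the situation where adjustment is most wanted and least informative.
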